## Methods/design

### Study design

The study design includes a prospective quantitative analysis and a related explorative qualitative analysis (see Fig. 1).

**Fig. 1 Fig1:**
[figure not shown]
Study design

The *prospective multicentre study* will (a) compare two cohorts of major trauma patients, those treated in maximum care facilities vs. those treated in standard care facilities, (b) compare results of the two cohorts with historical controls derived from the German Trauma Register DGU^®^ 2008 reference data and (c) compare results of the two cohorts with benchmarks including 5 outcome standards derived from the S3 guideline: risk adjusted morality (<15 %), door to CT-time (<20 min), ventilator free days (>22 days), ICU free days (>20 days), GOS (>80 % excellent and good).

The *qualitative part of the study* will (d) develop a service mapping tool (“blueprinting”) derived from quality management in the service industry in order to structure and visualize the care process for major trauma patients in the TNO, and (e) employ focus group discussions for identifying barriers and facilitators during the process, which can serve to explain why benchmarks are or are not met. This design allows for a comprehensive evaluation of TNO. In addition, the triangulation of methods provides for a profound understanding of the processes involved in acute major trauma care as well as the causal relationship between processes, structures and patient outcome. Whereas the quantitative study supplies data of patient outcome, and allows for comparisons between different health care standards plus the comparison of these results to benchmarks, the additional qualitative data provide an aid to interpretation and thus help in using the data for improvement of care processes and quality of care.

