## Abstract

**Background:**

The aim of this study is to evaluate the performance of the first certified regional trauma network in Germany, the Trauma Network Eastern Bavaria (TNO) addressing the following specific research questions: Do standard and maximum care facilities produce comparable (risk-adjusted) levels of patient outcome? Does TNO outperform reference data provided by the German Trauma Register 2008? Does TNO comply with selected benchmarks derived from the S3 practice guideline? Which barriers and facilitators can be identified in the health care delivery processes for polytrauma patients?

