### Current state of research

The German Trauma Society (Deutsche Gesellschaft für Unfallchirurgie, DGU) started a nationwide multicentre study based on voluntary participation of trauma centres in 1993. This registry data collection currently contains some 160.000 cases with over 130 single items per patient until December 2013. The aim of this trauma registry was to analyse the performance of individual trauma centres, including the pre-hospital management, the clinical care setting, and outcome data. The main results of the Trauma Register DGU® [4] were published and served as the empirical and conceptual basis for the “White Book of the Severely Injured Patient” (2nd ed, 2012, [5]).

The White Book delineated the creation of a nationwide system of regional trauma networks. Similar to the American trauma system, a ranking of trauma facilities was introduced where all participating hospitals were classified into basic, (“Lokales Traumazentrum”, comparable to US level III), standard (“Regionales Traumazentrum”, comparable to US level II), and maximum (“Überregionales Traumazentrum”, comparable to US level I) care facilities. Strict rules for patient transfer were introduced with the aim to "get the right patient at the right time to the right hospital". According to the White Book the maximum transportation time for a major trauma patient from the scene should not exceed 30 minutes. The patient has to be transported to the next available standard or maximum care facility. If this time interval cannot be adhered to (either by ground or air transportation), the nearest basic trauma facility has to initially stabilize the patient and then transfer him/her as soon as possible to the next higher level of care institution. All hospitals within a region were audited and the network was not certified until an agreement on cooperation and uniform patient documentation was signed and the German S3 guideline on polytrauma care [6] has been implemented.

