### Aim of the study

The aim of the present project is to evaluate the performance of the first certified regional trauma network in Germany, the Trauma Network Eastern Bavaria (TNO). In order to assess *qual*it*y* of care for *poly*trauma (*POLYQUALY*) the following specific research questions will be addressed:Do standard and maximum care facilities produce comparable (risk-adjusted) levels of patient outcome?Does network formation like the TNO outperform reference data provided by the German Trauma Register DGU^®^ 2008?Does TNO comply with selected benchmarks derived from the S3 practice guideline?What barriers and facilitators in the process of delivering health care to major trauma patients can be identified? How can these factors explain the results in patient outcome?

We hypothesize that the quality of care and therefore the outcome will be equal in hospitals with standard care in comparison to hospitals with maximum care facilities in a region if all hospitals are organized into a network structure that allows mutual support including the use of latest technologies such as telemedicine consultation. Furthermore, we hypothesize that TNO outperforms German Trauma Register DGU^®^ 2008 reference data and that the quality of care in the standard and maximum care facilities of TNO complies with guideline-derived benchmarks. In case our hypotheses hold true the qualitative barriers and facilitators analysis will be able to explain what the driving forces were that made this favorable results possible. In case the study results contradict our hypotheses the barriers and facilitators analysis can explain the hindering forces and may show ways how to improve the health care situation in the region.

The present project will also consider gender aspects. The majority of trauma patients (about 70 %) are male. In this study males and females will be enrolled according to the actual incidence of trauma events. After major trauma, quality of life differs between genders. Women have a 2.5 fold greater risk than men for developing psychological problems following major trauma and intensive care treatment (post-traumatic stress disorder, PTSD) [18, 19]. In order to address these gender-specific differences, quality of life outcomes will be compared between males and females.

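### Research questions 2 and 3 are put to the whole network, but the planned register and benchmark comparisons name only the maximum and standard care cohorts and state no whole-network result

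*Protocol article*

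**What the plan says.** **The questions.** The abstract asks "Does TNO comply with selected benchmarks derived from the S3 practice guideline". The Aim of the study section repeats this and asks "Does network formation like the TNO outperform reference data provided by the German Trauma Register". Both questions are about the network.

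**The hypotheses.** In Aim of the study, the register hypothesis stays with TNO. The benchmark hypothesis is narrower: "the quality of care in the standard and maximum care facilities of TNO complies with guideline-derived benchmarks".

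**The patients.** Study population and sampling recruits in all 25 TNO hospitals and includes patients with ISS of 16 or more treated at any of them. It expects 800 patients to be included and analysed.

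**The comparisons.** Study design, item (a), defines two cohorts: "those treated in maximum care facilities vs. those treated in standard care facilities". Item (b) will "compare results of the two cohorts with historical controls derived from the German Trauma Register". Item (c) will "compare results of the two cohorts with benchmarks including 5 outcome standards derived from the S3 guideline". The mortality standard in item (c) is risk-adjusted and set below 15 per cent.

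**The role of basic hospitals.** Under Current state of research, when the 30-minute transport limit cannot be kept, "the nearest basic trauma facility has to initially stabilize the patient", with onward transfer as soon as possible.

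**The statistical section.** Descriptive results are to be compared with the register and the benchmarks. No unit is named.

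**The concern.** The unit in the questions differs from the unit in the comparisons. The questions, the register hypothesis and the inclusion rule cover the network. Items (b) and (c) cover the patients of two of its three levels of care.

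Two consequences follow if items (b) and (c) are carried out as written:

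- Patients whose care begins and ends in a basic hospital are eligible and recruited, but count neither for nor against TNO. They include patients who die before transfer. First stabilisation and transfer are part of what the network is meant to organise, so a statement about TNO that omits this group is incomplete.
- Each benchmark yields two results, one per cohort. If one cohort meets a benchmark and the other does not, the plan does not say how the question about TNO is answered.

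This differs from bias in the standard-versus-maximum contrast. It would remain even if every patient in those two cohorts were assigned correctly.

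**Working it through.** **Step 1: unit of assessment, section by section**

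| Place | Unit |
|---|---|
| Abstract and Aim of the study, questions 2 and 3 | TNO |
| Aim of the study, register hypothesis | TNO |
| Aim of the study, benchmark hypothesis | standard and maximum care facilities |
| Study population and sampling | any of the 25 hospitals |
| Study design, items (b) and (c) | maximum and standard care cohorts |
| Abstract (Method/design), on register and guideline | not named |
| Biostatistical concept / statistical analysis | not named |

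For question 2, question and hypothesis agree with each other and differ from item (b). For question 3, hypothesis and item (c) agree with each other and differ from the question. No section states a pooled TNO result or a basic-hospital result.

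**Step 2: hospitals by level (Table 1)**

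2 maximum + 8 standard + 15 basic = 25. The two cohort levels account for 2 + 8 = 10 hospitals; the other 15/25 = 60% are basic. This is a share of sites, not of patients.

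**Step 3: where each patient goes under items (a) to (c)**

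- Treated directly in a maximum or standard hospital: in a cohort.
- First treated in a basic hospital, then transferred: can count in the receiving hospital's cohort, since forms can be matched (Quality assurance and safety).
- Treated only in a basic hospital and survives: in neither cohort.
- Dies in a basic hospital before transfer: in neither cohort.

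The gap is therefore the last two groups. The documents do not give their number.

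**Step 4: the plan's own figure**

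800 of 1,100 is 800/1,100 = 72.7%. It is a projection from register data. It is not divided by level of care and cannot be re-derived from stated inputs.

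**Step 5: illustration on assumed values**

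All rates here are crude, whereas the benchmark is risk-adjusted. The number and mortality of basic-only patients are assumptions.

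*Effect of leaving out 80 basic-only patients when the network has 120/800 = 15.0%:*

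- 20 deaths among the 80 (25%): cohorts show (120 − 20)/(800 − 80) = 100/720 = 13.9%.
- 12 deaths (15%): (120 − 12)/720 = 108/720 = 15.0%, no change.
- 4 deaths (5%): (120 − 4)/720 = 116/720 = 16.1%.

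The direction depends on whether basic-only mortality lies above or below the network's.

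*Basic-only mortality at which the whole network reaches 15%.* Let f be the share of the 800 treated only in a basic hospital and p the crude mortality in the two cohorts together. Network mortality is (1 − f) × p + f × m. Setting this to 0.15 gives m = [0.15 × 800 − p × 800 × (1 − f)] / (800 × f).

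| p | f | basic-only patients | m | deaths |
|---|---|---|---|---|
| 14% | 2% | 16 | (120 − 109.76)/16 = 64% | 10.2 |
| 14% | 5% | 40 | (120 − 106.4)/40 = 34% | 13.6 |
| 14% | 10% | 80 | (120 − 100.8)/80 = 24% | 19.2 |
| 13% | 2% | 16 | (120 − 101.92)/16 = 113%, not reachable | – |
| 13% | 5% | 40 | (120 − 98.8)/40 = 53% | 21.2 |
| 13% | 10% | 80 | (120 − 93.6)/80 = 33% | 26.4 |

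If the cohorts lie just below the limit, some 10 to 19 deaths among 16 to 80 basic-only patients would bring the network to it. If the cohorts lie clearly below it and few patients end their care in basic hospitals, the result would not change.

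**The case against.** The strongest reply is that nothing in the article excludes basic-hospital patients. All 800 are expected to be included and analysed, and the statistical section does not confine its comparisons to two cohorts. A fuller protocol or the analysis plan may provide a pooled result. The content of Fig. 1 and Fig. 2 was not available for this check, and Fig. 2 may show how these patients are handled. A reader might infer from items (b) and (c) that deaths in basic hospitals can never count against the network. **The documents do not support that.** It is what the two items say when read alone, and a whole-network comparison is not ruled out. Transferred patients who die later can also count in a cohort. What stands is that the article names the unit of comparison twice, and it is not the unit of its questions.

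For question 3, the benchmark hypothesis already has the narrower scope, and item (c) matches it. This is correct. It moves the contradiction to question against hypothesis, which still needs resolving.

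A reader might also infer that the plan is biased in the network's favour. That does not follow. The benchmark is risk-adjusted, so adjustment may absorb some or all of a higher crude mortality among basic-only patients. For the register comparison, the direction further depends on whether the 2008 data contain comparable early deaths in local hospitals, which the documents do not say. Scenarios that place the network exactly at 15% make any omission look decisive.

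Finally, results by level of care are informative, and a pooled figure alone could hide a weak level. This stands: there is no reason to remove the cohort results from questions 2 and 3.

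**Conclusion.** The point holds as a mismatch of scope. Questions 2 and 3 and the register hypothesis concern TNO, and inclusion covers all 25 hospitals. Items (b) and (c) name only the maximum and standard care cohorts. Taken literally, patients treated only in a basic hospital enter neither comparison, and no stated result answers the question about the network. The benchmark hypothesis and question 3 also differ in scope.

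The size and direction of any effect cannot be derived from the documents. Leaving out early deaths would flatter the network on the mortality benchmark if basic-only patients have higher risk-adjusted mortality than the rest. The crude figures, such as 13.9% against 15.0%, rest on assumed numbers and show scale only. The point is worth correcting because the remedy is cheap and the conclusion about the network depends on it. It does not show that the verdict on TNO would be wrong.

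**What to change.** In Study design, items (b) and (c), add a pooled TNO estimate for the register comparison and for each benchmark, and name it as the result that answers questions 2 and 3. It should cover every included patient, count each once across matched forms, and include those treated only in a basic hospital. Keep the maximum and standard care results, and add the basic-only group, as a breakdown beneath it. Bring question 3 and the benchmark hypothesis to the same scope.

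If a pooled estimate is not wanted, restrict the wording of questions 2 and 3, the register hypothesis and the conclusions to standard and maximum care facilities.

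The cost is a change of wording and one extra estimate per comparison. The clinical form is already mandatory in participating hospitals (Methods against bias), and forms of transferred patients can already be matched, so no new clinical data are needed. The pooled result may be less favourable than the two cohort results.

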### Study population and sampling

Patients will be recruited within the 25 hospitals that comprise TNO (Table 1). Inclusion criteria for the *prospective cohort study* are: major trauma ISS ≥ 16 (Injury Severity Score), treatment in any of the care facilities within the trauma network TNO, no age limitations. Exclusion criteria are ISS < 16, care outside TNO. Based on current register data it is expected that *n* = 1.100 patients will be assessed for eligibility and n = 800 be included and analyzed. For the *qualitative analysis* of barriers and facilitators, focus groups will be conducted with representatives of different professional groups involved in the TNO including emergency physicians, paramedics, dispatch centre staff, emergency room staff, trauma surgeons, rehabilitation staff and social workers. The focus group methodology can be transferred to other trauma networks and can be spread throughout Germany.

**Table 1 Tab1:** Trauma Network Eastern Bavaria / recruiting centres

Centre	Level of care
University Hospital Regensburg	Maximum Care Facility
Krankenhaus der Barmherzigen Brüder Regensburg	Maximum Care Facility
Klinikum Amberg	Standard Care Facility
Klinikum Eggenfelden	Standard Care Facility
Klinikum Deggendorf	Standard Care Facility
Klinikum Landshut-Achdorf	Standard Care Facility
Klinikum Neumarkt	Standard Care Facility
Klinikum Passau	Standard Care Facility
Klinikum Straubing	Standard Care Facility
Klinikum Weiden	Standard Care Facility
Krankenhaus Bogen	Basic Care Facility
Krankenhaus Burglengenfeld	Basic Care Facility
Krankenhaus Cham	Basic Care Facility
Krankenhaus Dingolfing	Basic Care Facility
Krankenhaus Freyung	Basic Care Facility
Krankenhaus Kelheim	Basic Care Facility
Krankenhaus Mallersdorf	Basic Care Facility
Krankenhaus Marktredwitz	Basic Care Facility
Krankenhaus St. Josef Regensburg	Basic Care Facility
Krankenhaus Schwandorf	Basic Care Facility
Krankenhaus Viechtach	Basic Care Facility
Krankenhaus Vilsbiburg	Basic Care Facility
Krankenhaus Vilshofen	Basic Care Facility
Krankenhaus Waldkirchen	Basic Care Facility
Krankenhaus Zwiesel	Basic Care Facility

### Data collection

Clinical information will be collected using the TraumaRegister^QM^ form. This quality management (QM) form underwent a rigorous development process and has been issued by the German Trauma Society. TraumaRegister^QM^ is a one-page, 40-item short form that includes among other things the following contents: date and site of referral, type of trauma, pre-hospital management, Glasgow Coma Scale (GCS), in-hospital management, ICU management and outcome at discharge (Glasgow Outcome Scale, GOS). A number of validated scores can be delineated from this documentation, such as AIS, ISS, TRISS, RISC, [20] for evaluation of adjusted outcome. TraumaRegister^QM^ will be completed by the participating hospitals via a web-based system. Data will be transferred to AUC (Akademie der Unfallchirurgie) and from there to the Centre for Clinical Studies Regensburg.

Another data source which will be used as a historical control is the German Trauma Register DGU^®^ reference data base. Quality of life will be assessed using the EQ-5D form which is a short form widely used in large scale cohort studies. This instrument underwent rigorous psychometric testing, is part of the trauma-specific QL measurement system POLO-Chart [21] and generates indices that can be used for further socio-economic analyses. A German version and population-based German reference data are available. EQ-5D assessment will be performed 6, 12 and 24 months after trauma (Fig. 2). Assignment to the respective clinical information documented in TraumaRegister^QM^ will be accomplished via an index number.

**Fig. 2 Fig2:**
[figure not shown]
Algorithm patient flow

In the course of the qualitative part of this project the semi-standardized interviews and focus groups will be conducted face-to-face, audio-taped and transcribed verbatim. For the analysis of barriers and facilitators, the developed blueprint will be used as a basis for focus group discussions.

### Methods against bias

The use of TraumaRegister^QM^ is mandatory for participating hospitals via the TNO contract and hospital staff will be trained to complete the form via a web-based system. Non-compliant hospitals are easily detectable. Assistance with data collection and checks on plausibility will be provided by a data manager hired for this study and affiliated with the Centre for Clinical Studies at the University Hospital Regensburg. Thus, a near complete (>95 %) documentation of all major trauma patients with a minimum of missing values for the two-year recruitment period can be expected. The quality management of the *qualitative data* collection and analysis will be performed according to the standards set by [22]. Among others, it is planned to utilize “respondent validation” by presenting the results and discussing them with interviewees and focus group members in interactive workshops.

### Biostatistical concept / statistical analysis

*Prospective cohort study*: Statistical analyses of the prospective data will primarily dwell on descriptive statistics using counts, percentages, means/standard deviations, medians/interquartiles/ranges and confidence intervals. In order to interpret descriptive results they will be compared with secondary data from the Trauma Register DGU^®^ reference data bank 2008 and the benchmarks derived from the S3 guideline on major trauma. A logistic regression will be performed with 30 day mortality as the dependent variable and the ISS and TRISS scores as covariates. A p value of < 0.05 will be considered statistically significant. All other statistical tests will be chosen according to the scale level of the variable and the number of variables used in the model (t-test, Mann–Whitney U-Test, chi-squared test, risk-adjusted multivariable regression models) and will be performed in an explanatory manner, leaving alpha at < 0.05.

*Qualitative study*: Interview and focus group transcripts will be critically examined using thematic content analysis [23]. Themes will be identified using a grounded conceptualisation process [24]. Transcripts will be repeatedly read before and after coding to ensure proper categorisation of data. For the blueprint, the information on the health care process will be visualized as a two-dimensional picture: The horizontal axis represents the chronology of actions by the patient and the health care professional. The vertical axis distinguishes between different areas of actions, i.e. direct interactions between patient and professional, professional actions visible and invisible to the patient, support processes, and planning, managing and controlling activities [15, 17].

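### The comparison with the 2008 register cannot attribute a difference to network formation: network and calendar time coincide, and no case-mix adjustment is assigned to it

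*Protocol article*

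**What the plan says.** The Aim of the study section puts the question in terms of an effect of networks: "Does network formation like the TNO outperform reference data provided by the German Trauma Register" for 2008. The hypothesis that follows is directional: "Furthermore, we hypothesize that TNO outperforms German Trauma Register" 2008 reference data.

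The Study design section names the type of control. The study will "compare results of the two cohorts with historical controls derived from the German Trauma Register", again the 2008 data.

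The section Biostatistical concept / statistical analysis supplies the method. "Statistical analyses of the prospective data will primarily dwell on descriptive statistics", and then "In order to interpret descriptive results they will be compared with secondary data from the Trauma Register" 2008 and with the guideline benchmarks. The one model set out there is a logistic regression of 30-day mortality on ISS and TRISS. It has no term for TNO versus register and none for period.

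Risk adjustment is mentioned in four places, none tied to the register:

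- The first research question: "Do standard and maximum care facilities produce comparable (risk-adjusted) levels of patient outcome".
- The mortality benchmark in Study design.
- Data collection, which says that TRISS, RISC and other scores can be derived from the form to evaluate adjusted outcome.
- The statistics section, where risk-adjusted regression models appear in a general list of other tests.

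**The concern.** A claim that forming a network improved outcome needs a comparison in which the network is the main thing that differs. Here the two groups also differ entirely in calendar time. If mortality after major trauma fell in Germany between 2008 and the recruitment years for any other reason, TNO would look better whether or not the network did anything. If recording or referral changed so that later patients were sicker on average, a real benefit could be hidden.

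The article itself notes, under Current state of research, that the effect of networks on quality of care is unsettled. Under Discussion it directs the results to ministries, insurers and professional societies nationwide. A favourable contrast with 2008 could be taken there as evidence that networks work, which this comparison cannot show.

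**Working it through.** **Step 1: is calendar time separable from the network?** The reference data are from 2008. The TNO data are prospective. Recruitment lasts two years and its dates are not given, but the documentation form has been in routine use since 2009 (Abstract) and the earlier registration is dated 10 January 2013. No concurrent comparator from outside the network appears anywhere in the article. So network status and period take the same values in every patient: TNO and later, or register and 2008. A regression with a term for each cannot be estimated, and a severity score does not help because it measures injury, not era.

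**Step 2: is case mix handled?** The first research question carries the words risk-adjusted and the second does not. The statistics section speaks of comparing descriptive results. Adjustment is thus unspecified for this contrast, while the means for it exist. TNO patients must have ISS ≥ 16; no ISS limit is stated for the 2008 reference set.

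**Step 3: how large could the effect of time be?** The plan gives no power, margin or register mortality, so there is no figure to reproduce. What follows is illustration.

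Inputs:

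- n = 800 analysed patients (Study population and sampling).
- Reference mortality 15%. This is an assumption, borrowed from the article's benchmark for risk-adjusted mortality. The register's 2008 rate is not given.
- Reference rate treated as fixed, and a two-sided test at 0.05. Both are assumptions: the article sets alpha at 0.05 without stating sidedness and assigns no test to this contrast.
- Gap of 5 years and a secular fall of 0.3 to 0.5 points a year, that is 1.5 to 2.5 points. Both are assumptions.

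Standard error: √(0.15 × 0.85 / 800) = 0.0126, so the 95% half-width is 1.96 × 0.0126 = 2.5 points.

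Probability that a network with no effect looks significantly better: Φ(shift / 0.0126 − 1.96).

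| Secular fall | Probability |
|---|---|
| none | 0.025 |
| 1.5 points | 0.22 |
| 2.0 points | 0.35 |
| 2.5 points | 0.51 |

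**Step 4: sensitivity to the form of the drift.** Let mortality fall by a fixed proportion r a year for 5 years, p₁ = 0.15 × (1 − r)⁵. Use Φ((0.15 − p₁ − 1.96 × SE₀) / SE₁), with SE₀ computed at 15% and SE₁ at p₁. The last column replaces the fixed reference by an assumed 4,000 register patients.

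| r per year | p₁ | Fixed reference | 4,000 reference patients |
|---|---|---|---|
| 2% | 13.6% | 0.197 | 0.174 |
| 4% | 12.2% | 0.601 | 0.529 |
| 6% | 11.0% | 0.915 | 0.858 |

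**Step 5: what an unadjusted case-mix difference could do.** Assume two severity strata with mortality 8% and 35%. With 30% of patients in the severe stratum, crude mortality is 0.70 × 8% + 0.30 × 35% = 16.1%. With 20%, it is 0.80 × 8% + 0.20 × 35% = 13.4%. With the same formula, and 16.1% as the reference, the probability of apparent superiority is 0.55. The strata and shares are invented for illustration.

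**The case against.** The strongest reply is that the article is open about what it does. It calls the comparator historical, states a hypothesis and not a finding, describes the analysis as mainly descriptive, and uses the register to help interpret results. A condensed article may leave the adjustment model to a fuller plan. The first research question and the guideline benchmarks are untouched.

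Much of this stands, and it rules out several stronger readings that a reader might infer:

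- *That the plan excludes case-mix adjustment.* It does not. The scores are named and adjusted models are listed in general terms. The text only fails to assign them to this contrast.
- *That case mix is as inseparable from the network as calendar time.* It is not. Severity is measured and can be adjusted for.
- *That the two populations are shown to differ in severity.* They are not. The article does not describe the 2008 set's ISS distribution. Voluntary participation of centres says which hospitals joined, not which patients were recorded.
- *That the percentages are an error rate of this plan.* They are not. The test, the time gap, the drift and the base rate are all supplied from outside.

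It is also fair to say that a same-period register comparison does not answer the question as worded. The article describes a nationwide system of regional networks, so later register data may contain other networked hospitals.

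What the reply does not meet is the time problem. The 2008 comparator is stated in the aim, the design and the statistics section. An analysis plan could not separate period from network without changing that comparator. Labelling the control as historical does not limit the conclusion while the question still speaks of network formation.

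**Conclusion.** The point holds for attribution. Followed as written, the comparison can show that TNO patients did better or worse than the 2008 reference. It cannot show that forming the network was the reason. This follows from the stated design and depends on no figure.

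On case mix the conclusion is narrower: adjustment is possible and not ruled out, but it is not tied to this comparison and should be.

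As to size, a purely secular fall of 1.5 to 2.5 points would make a network with no effect look significantly better in about 22% to 51% of studies of 800. Relative falls of 2% to 6% a year over 5 years give about 20% to 92% against a fixed reference. These ranges show only that plausible-looking drift is of the same order as the 2.5-point half-width. The documents do not say that such a drift occurred. The consequence is confined to the second research question.

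**What to change.** Three changes, none of which affects enrolment or data collection:

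1. **Statistics section.** Restrict the register reference to ISS ≥ 16, exclude any TNO hospitals from it, and base the mortality comparison on the ratio of observed to RISC-expected deaths with 95% confidence intervals for TNO and for the register, in place of crude descriptives. Use one definition of mortality in both sources, and check that the 2008 extract holds the items RISC needs.
2. **Supportive analysis.** Add a register extract for the same calendar years as TNO recruitment, analysed in the same way, to show the secular trend. State that it may include other networks, so it tests TNO against contemporaneous German care and not network against no network.
3. **Aim and conclusion.** Reword the second question and its hypothesis so that the 2008 contrast is reported as a before-after difference that is not attributable to the network alone.

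The cost is one further register extract, modest analysis work, and a weaker permitted conclusion. The first change deals with measured severity only. The third is the one that deals with calendar time, with the second showing how much it might matter.
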